### Analysis

An interim analysis will be performed after 20 patients have been accrued. This will correspond to an estimated 10 intervention events over 100 sessions. If four or fewer responses are observed in these 10 events, consideration will be given to the cause of the lack of response and the study may be stopped on the grounds of futility. At the same time, the IDSMC will review the trial for safety and determine whether or not it should continue. Otherwise, the study will continue with an additional 28 patients to be recruited. The main analysis will be performed after all 48 patients have completed treatment, with the final analysis being performed after the last patient has completed 2 years of follow up.

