### Sample size calculation

We will enrol 48 patients to test the hypothesis that patient dose distributions are improved with the use of the KIM technology. The derivation follow: treating each treatment session as an independent event and then using Simon’s two-stage design, a sample size of 24 sessions with intervention events will give us 90% power with 95% confidence to rule in a success rate of 2/3 in favour of the futile rate of 1/3. To obtain an estimated 24 treatment sessions with intervention events we need 24/0.10 = 240 treatment sessions, which for the 5-session SBRT regime equals 48 patients. The null hypothesis will be rejected if 16 or more responses are observed in 48 patients. This design yields a type I error rate of 0.0488 and power of 0.91 when the true response rate is 67%.

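### The stated alpha of 0.0488 and power of 0.91 need exactly 10 and 24 intervention events, but the looks are timed by patients with fixed response counts and no rule for other event numbers

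*Protocol article*

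**What the plan says.** The Sample size calculation section works in intervention sessions: "a sample size of 24 sessions with intervention events will give us 90% power with 95% confidence". The two success rates set against each other are 2/3 and 1/3, and the derivation rests on "treating each treatment session as an independent event". It converts events to patients through an assumed 10% event rate: "To obtain an estimated 24 treatment sessions with intervention events we need 24/0.10 = 240 treatment sessions", which is 48 patients at five sessions each. The final rule is "The null hypothesis will be rejected if 16 or more responses are observed in 48 patients", with these properties: "This design yields a type I error rate of 0.0488 and power of 0.91 when the true response rate is 67" per cent.

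The Analysis section times the looks by patients. The interim rule is "An interim analysis will be performed after 20 patients have been accrued", which is said to correspond to an estimated 10 events in 100 sessions. The futility condition reads "If four or fewer responses are observed in these 10 events". Meeting it leads to consideration of the cause, and stopping is optional. The main analysis takes place when the 48 patients have been treated.

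**The concern.** A Simon boundary is a response count attached to a fixed number of observations. Here the observations are intervention events, and the looks come at fixed numbers of patients. How many events have occurred by then is a matter of chance and of an event rate that the article itself calls an estimate.

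Four responses are poor in 10 events, good in 5 or 6, and very poor in 15. A fixed final count has the same weakness. The article gives no cut-off for an event count other than the planned one. The printed error rates are therefore not those of the trial as it will be run, and the primary hypothesis test rests on them.

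**Working it through.** **Inputs from the article.** p0 = 1/3; p1 = 2/3; event rate q = 0.10 per session; independent sessions; 100 sessions at the interim and 240 in all (140 after the interim); futility at <=4 responses.

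**1. Reproduce the stated figures.** With exactly 10 then 24 events and a binding stop, P(reject) = sum over x = 5 to 10 of Bin(x; 10, p) × P(Bin(14, p) >= c − x).
- c = 12: alpha 0.0488 and power 0.911 with p0 = 0.333 and p1 = 0.667 (0.0492 and 0.910 with exact thirds). This is the Simon optimal design for these inputs, so the stated figures are recovered.
- c = 16, the printed cut-off, on the same 24 events: 0.0008 and 0.588. Read literally as 16 of 48 in a single stage: 0.554 and above 0.999. Neither matches.
- c = 12 of 24 with the stop ignored: alpha 0.068. The 0.0488 therefore also needs the stop to be obeyed.

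**2. How variable is the event count?** At q = 0.10 the interim count is Bin(100, 0.10): exactly 10 with probability 0.13, 95% range 5 to 16. The final count is Bin(240, 0.10): exactly 24 with probability 0.09, 95% range 15 to 33, and below 24 with probability 0.47.

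**3. Chance of <=4 responses when p = 2/3, by number of interim events.** For 10 events it is (1 + 20 + 180 + 960 + 3360)/3^10 = 4521/59049 = 0.077.

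| Events | 5 | 6 | 8 | 10 | 12 |
|---|---|---|---|---|---|
| P(<=4) | 0.87 | 0.65 | 0.26 | 0.077 | 0.019 |

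**4. Average over the event count.** Each session yields a response with probability q × p, so interim responses are Bin(100, 0.10 × 2/3) = Bin(100, 0.0667), and P(<=4) = 0.196. Under the null the criterion is met with probability 0.76 instead of 0.79.

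Event rates other than 10% are assumptions, to show the range:

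| Event rate | 7% | 8% | 10% | 12% | 15% |
|---|---|---|---|---|---|
| P(<=4), p = 2/3 | 0.50 | 0.38 | 0.196 | 0.09 | 0.02 |

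An assumed within-patient correlation of events of 0.1 to 0.3 raises the 10% figure to about 0.23 to 0.28.

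**5. Whole design at q = 0.10.** Interim responses are Bin(100, 0.10p) and later responses Bin(140, 0.10p).

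| Final cut-off | Stop binding: alpha / power | Stop ignored: alpha / power |
|---|---|---|
| 12 | 0.075 / 0.758 | 0.108 / 0.881 |
| 16 (printed) | 0.006 / 0.503 | 0.007 / 0.537 |

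With cut-off 12 and the stop ignored, power falls to 0.54 at an event rate of 7.5%, and alpha rises to 0.54 at 15%.

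**6. Candidate repairs.** Futility at <=40% of observed events, treated as binding:

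| Final rule | 5% | 7.5% | 10% | 15% |
|---|---|---|---|---|
| Exact binomial cut-off: alpha | – | 0.029 | 0.029 | 0.029 |
| Exact binomial cut-off: power | – | 0.80 | 0.89 | 0.97 |
| Responses >=50% of events: alpha | 0.116 | 0.074 | 0.049 | – |

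At q = 0.10 the 40% rule is met with probability 0.058 when p = 2/3 and 0.70 when p = 1/3.

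**The case against.** Three stronger readings are tempting, and the article supports none of them.

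- **That an effective KIM would be wrongly stopped 20% of the time.** The rule is non-binding. The 20% is the chance of meeting a condition that prompts a review, and so an upper limit on wrongful stopping. The 8% has the same status, so the comparison between them stands.
- **That the count of 4 governs whatever the number of events.** The text ties it to 10 events and is silent otherwise. A team seeing 4 responses in 5 events would hardly call that a failure. The supportable criticism is that no rule is given for other counts; the 20% shows what follows if the printed count is carried over.
- **That fewer than 100 sessions will have been delivered at the interim.** The article speaks of accrual but equates the look with 100 sessions, so the intent is probably 20 fully treated patients. If only 80 had been delivered, the probability would be 0.38, but the 80 is an assumption without a source. What stands is that the trigger is loosely worded.

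It is also fair to say that random event counts are not the only reason the error rates fail. Under the printed cut-off of 16, power is already 0.588 with exactly 10 and 24 events, and randomness lowers it only to 0.503. Correcting 16 to 12 would still leave the problem described here.

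A full protocol might adapt the cut-offs. But the article itself states the triggers, the counts and the error rates, and these do not fit together.

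**Conclusion.** The point holds. The stated 0.0488 and 0.91 are properties of a design with exactly 10 and 24 events, cut-offs <=4 and >=12, and an obeyed stop. They are not properties of looks at 20 and 48 patients with fixed counts. The size of the effect rests on a 10% event rate, independent sessions and the count of 4 being used regardless of events. On that basis the chance that an effective KIM meets the futility criterion rises from about 8% to about 20%. With a final cut-off of 12, alpha exceeds 0.05 whether or not the stop is obeyed. No single figure should be taken as firm, because the result moves steeply with the event rate. The mismatch between trigger and boundary does not depend on that rate.

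**What to change.** Keep 48 patients and write the rules in terms of the observed number of intervention sessions:

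- **Final analysis:** reject at the exact one-sided 5% binomial cut-off against 1/3 for the observed number of events (13 if there are 24). This keeps alpha at or below 0.05, under independent sessions, whether or not the futility stop is followed.
- **Interim:** state futility as responses in <=40% of observed events, and hold the look once the first 20 patients have completed treatment.
- **Restate alpha and power:** about 0.03 and 0.89 at a 10% event rate, with power 0.80 at 7.5%.
- **Reconcile** the printed 16 and its denominator of 48 patients with whatever error rates are stated.

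A flat final rule of at least 50% of events should not be used, because its alpha exceeds 0.05 when events are fewer than expected.

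Alternatively, trigger the looks at the 10th and 24th intervention sessions with cut-offs <=4 and >=12. That restores the stated figures if the stop is obeyed, but at a 10% rate there is a 47% chance that 48 patients yield fewer than 24 events.

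The main option costs wording, a slightly later interim and a slightly lower stated power. It needs no extra patients.

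### The stated type I error of 0.0488 relies on a binding futility stop at 4 or fewer of 10 events, but the plan makes that stop optional

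*Protocol article*

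**What the plan says.** The Sample size calculation section of the protocol article treats sessions as independent and sets the design: "using Simon’s two-stage design, a sample size of 24 sessions with intervention events will give us 90% power with 95% confidence". The two rates being compared appear in the same sentence, where the aim of the test is given as "to rule in a success rate of 2/3 in favour of the futile rate of 1/3". The section then gives the operating characteristics: "This design yields a type I error rate of 0.0488 and power of 0.91 when the true response rate is 67" per cent. The printed final rule is "The null hypothesis will be rejected if 16 or more responses are observed in 48 patients".

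The Analysis section places the interim look after 20 patients: "This will correspond to an estimated 10 intervention events over 100 sessions". The futility condition is "If four or fewer responses are observed in these 10 events", and the consequence is that "consideration will be given to the cause of the lack of response and the study may be stopped on the grounds of futility".

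The article does not say what becomes of the hypothesis test if the study goes on after that condition is met.

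**The concern.** In a two-stage design of this kind, the quoted error rate normally counts every trial that falls at or below the interim boundary as a non-rejection. The word used here is permissive, and a low interim count leads first to a look at its cause. A trial that continues can still reach the final cut-off, and those extra routes to rejection add to the type I error. If 0.0488 was computed with the stop enforced, it takes credit for a rule that the plan does not impose. There is little room below 0.05 to absorb the difference. At stake is the 95% confidence claimed for the primary hypothesis.

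**Working it through.** **Inputs.** From Sample size calculation: p0 = 1/3, p1 = 2/3 (printed as 67%), N = 24 events, stated type I error 0.0488, power 0.91. From Analysis: n1 = 10 events, futility at 4 or fewer. The second stage therefore has 24 − 10 = 14 events.

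**Formulas** (exact binomial, independent events, final cut-off r):

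- Stop always applied: P(reject) = Σ over x = 5 to 10 of P(X1 = x) × P(X2 ≥ r − x), with X1 ~ Bin(10, p) and X2 ~ Bin(14, p).
- Stop never applied: P(reject) = P(X ≥ r), with X ~ Bin(24, p).

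**Step 1: reproduce the plan's figures.** With r = 12 and p0 = 0.333, the terms for x = 5, 6, 7, 8, 9, 10 are 0.02027 + 0.01752 + 0.00846 + 0.00223 + 0.00030 + 0.00002, which sum to 0.0488 from unrounded terms. With p0 = 1/3 unrounded the result is 0.0492. Power is 0.910 at 2/3 and 0.915 at 0.67, so 0.91 on either reading. A search over single-stage designs, and over two-stage designs with N up to 30 and power 0.90 to 0.92, found 0.0488 only for 4/10 then 12/24 with the stop enforced.

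**Step 2: remove the stop and keep r = 12.**

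| Handling of 4 or fewer of 10 | Type I error, p0 = 0.333 | Type I error, p0 = 1/3 |
|---|---|---|
| Always stop | 0.0488 | 0.0492 |
| Continue only at exactly 4 | 0.0618 | 0.0623 |
| Always continue | 0.0672 | 0.0677 |

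**Step 3: how much continuation passes 0.05?** Suppose the chance of continuing is the same for every count of 4 or fewer.

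- p0 = 0.333: (0.05 − 0.0488)/(0.0672 − 0.0488) = 0.0012/0.0184 ≈ 6.5%.
- p0 = 1/3: (0.05 − 0.0492)/(0.0677 − 0.0492) = 0.0008/0.0185 ≈ 4.5% (from unrounded values).

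That is roughly 5 to 7% of below-boundary cases.

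**Step 4: how often does it bite?** At p = 1/3, P(4 or fewer of 10) = 0.787. Given that, the chance of still reaching 12 of 24 is (0.0677 − 0.0492)/0.787 = 2.4%. The total addition to the type I error is at most 0.0677 − 0.0492 = 0.0185.

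**Step 5: try the printed boundary of 16.**

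| Reading | Type I error, stop applied | Type I error, no stop | Power |
|---|---|---|---|
| 16 of 24 events | 0.0008 | 0.0009 | about 0.59 to 0.61 |
| 16 of 48 binary outcomes | 0.17 | 0.55 | not needed |

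Neither reading gives 0.0488.

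**Step 6: a cut-off that tolerates discretion.** With r = 13 of 24 and p0 = 1/3, type I error is 0.0284 if never stopped, and lower if stopped. Power at 2/3 is 0.932 if never stopped and 0.885 (0.8845) if always stopped.

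**The case against.** **The printed cut-off is 16, not 12.** This stands as a limit on the point. The number 12 appears nowhere in the article and is inferred from the stated 0.0488 and 0.91. A reader might infer that the rule as printed breaches 5% because the stop is optional. The document does not support that. With 16 of 24 events the type I error is about 0.0009 even with no stop. With 16 of 48 binary outcomes it is already 0.17 with the stop enforced. In neither case does the stop decide whether 0.05 holds. The printed rule cannot rescue the stated figures either, and correcting it to 12 of 24 would leave the present problem in place.

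**The inflation is small and 0.068 is the extreme.** Also fair. A reader might take 0.068 as the trial's error rate, or take the 79% chance of meeting the futility condition at the futile rate as a measure of harm. But 0.068 needs continuation every time, and only 2.4% of below-boundary trials would go on to 12 of 24. What remains is that the margin below 0.05 is so thin that occasional continuation uses it up.

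**Optional futility stops are common and reasonable.** True, and a technical cause in a technology trial is a good reason to pause before stopping. The discretion itself is not the fault. An optional stop is compatible with error control when the final cut-off is set as if no stop occurred. Here the quoted error rate assumes the opposite.

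**Conclusion.** The point holds in conditional form. The stated 0.0488 and 0.91 belong to a design with a binding stop at 4 or fewer of 10 and rejection at 12 or more of 24, while the Analysis section makes that stop optional. Under this cut-off the type I error is somewhere from 0.049 to 0.068, depending on how the discretion is used, so the claimed 95% confidence is not guaranteed.

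This rests on the inferred cut-off of 12 of 24, on independent sessions as the protocol assumes, and on exactly 10 and 24 intervention events. The last condition matters because the looks are set by patients (20 and 48) and the event counts are only estimates. With a binding stop at 4 of 10 and the cut-off still at 12, 25 events would give 0.062 and 26 would give 0.075. The change is worth making, but the flaw does not undermine the trial as a whole.

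**What to change.** Correct two things together in the Sample size calculation and Analysis sections.

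1. Replace the printed final boundary with 12 or more responses in 24 intervention events.
2. Add that, if the study continues after 4 or fewer responses in the first 10 events, the null hypothesis cannot be rejected and the results are descriptive.

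This keeps the type I error at 0.049 and power at 0.91. It leaves the decision to stop or continue where it is and limits only what may be concluded afterwards. The cost is one corrected number and one added sentence, with no extra patients.

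Alternatively, keep the discretion with no limit on inference, set the boundary at 13 of 24, and restate the type I error as at most 0.028 and power as 0.88 to 0.93. The cost is that 0.88, reached if the stop is always applied, falls short of the 90% power the section promises, and this should be stated.

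Under either option, say that the figures apply to exactly 10 and 24 events.

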### Objectives

The primary objective is to quantify accumulated patient dose distributions with the KIM intervention compared to dose distributions estimated without the KIM intervention. Secondary objectives are to assess patient treatment outcomes, to perform a technology assessment of KIM to quantify the clinical practice impact, and to assess KIM cancer targeting accuracy.

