### Assessments

For each visit, prostate-specific antigen (PSA), GU and GI physician-graded toxicity (RTOG scale) and patient-reported outcomes using the Expanded Prostate Cancer Index Composite (EPIC) instrument will be recorded. Where possible, and noting the limitations of retrospective comparisons, different patient cohorts and differing eligibility criteria, outcome measures will be compared with controls in participating centres and with large published series, such as the 1100-patient pooled analysis by King [2, 3] and the 477-SBRT patient series from Katz [24].

Physician-reported acute toxicity will be measured during treatment, then after treatment completion at 2 weeks, 6 weeks, 3 months, 6 months and every 6 months thereafter until 3 years after treatment. Patient reported outcomes will be at baseline, then after treatment completion at 2 weeks, 6 weeks, year 1 and year 3. Biochemical control will be assessed with PSA testing at baseline, then after treatment completion at 6 weeks, 3 months, 6 months and every 6 months thereafter until 3 years after treatment. Biochemical failure is defined using the RTOG Phoenix definition [25] (any rise in the PSA >2 ng/L above the nadir). The estimated outcome improvements will be determined by applying established dose-response models to the patient’s accumulated dose and comparing with the estimated accumulated dose distribution in the absence of the KIM intervention.

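### The final analysis is triggered at the last patient's 2-year point, but outcomes are scheduled to 3 years, so year-3 EPIC and the month 30 and 36 visits are incomplete at that cut-off

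*Protocol article*

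**What the plan says.** The Analysis section names two analyses after the interim look. The first is tied to the end of treatment: "The main analysis will be performed after all 48 patients have completed treatment". The second is tied to follow-up: "with the final analysis being performed after the last patient has completed 2 years of follow up". The article describes no analysis after that.

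The Assessments section gives each outcome its own schedule:

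- Physician-graded toxicity: during treatment, then "at 2 weeks, 6 weeks, 3 months, 6 months and every 6 months thereafter until 3 years after treatment".
- Biochemical control: "PSA testing at baseline, then after treatment completion at 6 weeks, 3 months, 6 months and every 6 months thereafter until 3 years after treatment".
- EPIC: "Patient reported outcomes will be at baseline, then after treatment completion at 2 weeks, 6 weeks, year 1 and year 3".

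The same section opens with a general sentence: "For each visit, prostate-specific antigen (PSA), GU and GI physician-graded toxicity (RTOG scale) and patient-reported outcomes" are to be recorded. Read literally, it does not match the specific EPIC and PSA schedules that follow.

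Under Objectives, the comparison of dose distributions with and without KIM is primary. The outcomes at issue here are secondary: "Secondary objectives are to assess patient treatment outcomes". Improved patient outcome is also the second of the three hypotheses listed at the start of Methods/Design.

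**The concern.** The cut-off for the last analysis and the length of the assessment schedule are both stated, and they do not fit. The analysis called final comes a year before the last patient's last scheduled visit.

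The mismatch is sharpest for EPIC. After week 6 the specific schedule has only years 1 and 3, so no EPIC falls at the 2-year point that triggers the analysis. For the last patient, waiting from year 1 to year 2 adds toxicity and PSA visits but no patient-reported time point.

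What is at stake is the long-term part of a secondary objective. A year-3 EPIC summary at this cut-off would rest on a subset defined by treatment date, not on the whole cohort. The third-year data of later-treated patients would have no stated analysis. The Assessments section also intends comparisons with large published series, so the follow-up time to which each result refers should be clear.

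**Working it through.** No figure in the plan can be reproduced here, because the timing is a design choice. The check compares the schedule with the cut-off and then sizes the incomplete part.

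**Inputs**

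- Cut-off: last patient at 24 months (Analysis).
- Visit schedules (Assessments).
- N = 48 (Sample size calculation).
- Accrual time: not given, so treated as an assumption and varied.
- Follow-up is taken to run from treatment completion, as the visit times do.

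**Step 1. Post-treatment assessments due for every patient at the cut-off**

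| Outcome | Scheduled after treatment | Due for all 48 | Not due for the last patient |
|---|---|---|---|
| EPIC | 2 wk, 6 wk, 12, 36 mo (4) | 3 of 4, latest at 12 mo | 36 mo |
| Toxicity | 2 wk, 6 wk, 3, 6, 12, 18, 24, 30, 36 mo (9) | 7 of 9, latest at 24 mo | 30, 36 mo |
| PSA | 6 wk, 3, 6, 12, 18, 24, 30, 36 mo (8) | 6 of 8, latest at 24 mo | 30, 36 mo |

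**Step 2. Share of patients with year-3 data due**

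A patient treated t years before the last one has 2 + t years of follow-up at the cut-off. Year-3 data are due if 2 + t ≥ 3, that is t ≥ 1. With uniform accrual over A years the share is max(0, 1 − 1/A).

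| A (years, assumed) | Formula | Share | Count with 48 evenly spaced patients |
|---|---|---|---|
| 1 | 1 − 1/1 | 0% | 1 of 48 (the first patient, exactly on the boundary) |
| 1.5 | 1 − 1/1.5 | 33% | 16 of 48 |
| 2 | 1 − 1/2 | 50% | 24 of 48 |
| 3 | 1 − 1/3 | 67% | 32 of 48 |
| 4 | 1 − 1/4 | 75% | 36 of 48 |

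The share stays below 100% for any A, because everyone treated within a year of the last patient falls short.

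**Step 3. The month 30 visit**

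The condition is 2 + t ≥ 2.5, so t ≥ 0.5 and the share is max(0, 1 − 0.5/A): 50% for A = 1, 75% for A = 2 and 83% for A = 3. The loss is smaller than for year 3 but follows the same pattern.

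**Step 4. After the change**

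With the cut-off at the last patient's 3-year visit, 4 of 4 EPIC, 9 of 9 toxicity and 8 of 8 PSA assessments are due for everyone.

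**Step 5. The general visit sentence**

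Taken literally, it would put EPIC at the 2-year visit and PSA at the 2-week visit. The specific schedules contain neither. Step 1 uses the specific schedules, as the more detailed text. If the general sentence governed instead, a 2-year EPIC would be due for everyone and the statement about year 1 would not apply. Year 3 would still be incomplete.

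**The case against.** The strongest reply is that a common cut-off with a minimum follow-up of 24 months is ordinary practice. The Analysis section sets a minimum for the last patient and does not truncate earlier patients at 2 years. Biochemical failure is defined as an event, and time-to-event methods can use the later visits of earlier patients with censoring. The same can be done for late toxicity. This stands for PSA and largely for toxicity, so for those two outcomes the timing is closer to a preference. It does not help a questionnaire score taken at fixed times, where a year-3 summary needs the year-3 form.

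A second reply is that a journal article condenses a fuller protocol, so a 3-year report may be planned elsewhere. That is possible, and a reader should not infer that third-year data will go unreported, because the article does not say so. It does, however, call the 2-year analysis final, and the conflict is between two rules that it states itself.

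Three stronger readings are tempting and are not supported:

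- A reader might infer that long-term data miss the final analysis altogether. They do not: year-1 EPIC and toxicity and PSA to month 24 are due for all patients, and earlier-treated patients may already have year-3 data.
- A reader might infer that the early subset reflects a learning curve with KIM. The article gives no evidence that early patients differ. It can only be said that the subset is defined by treatment date.
- A reader might infer that the trial's main conclusion is weakened. The dose comparison is analysed once all patients have finished treatment, so it is untouched.

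On the general visit sentence, it is fair to say that it reads as a list of instruments and that the detailed schedules naturally govern.

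**Conclusion.** The mismatch is real and limited to secondary outcomes. With the specific schedules, the latest EPIC time point due for all 48 patients at the final analysis is year 1. Year-3 EPIC and the month 30 and 36 toxicity and PSA visits are incomplete. How incomplete depends on the accrual time, which the article does not give: under uniform accrual, year-3 data are due for about 0% of patients if accrual takes 1 year, 50% if 2 years and 67% if 3 years. These shares count visits that are due. Missed visits and dropout would lower them further.

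That year-3 data cannot be complete at this cut-off follows from the stated timings alone. The size rests on the accrual assumption, and the statement about year-1 EPIC rests on the specific schedule governing over the general sentence. The point should be corrected but does not threaten the primary result.

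**What to change.** In the Analysis section, set the final analysis of patient outcomes after the last patient's 3-year visit, and label the 2-year analysis as a planned earlier report that states which time points are complete for all patients. The data are already scheduled for collection. The cost is a final outcomes report up to one year later. The sample size, type I error and power belong to the dose question and do not change.

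If the 2-year analysis has to remain final, adding EPIC at the existing 2-year visit would give a patient-reported time point that matches the cut-off, at the cost of one more questionnaire per patient. The third-year data would still be incomplete, so this is the weaker option.

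As a minor editorial correction, reword the opening sentence of Assessments so that it points to the specific EPIC and PSA schedules and does not imply that every instrument is used at every visit.
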